#### Objectives and significance of proposed study

The studies reviewed above are suggestive of protective effects of folic acid supplementation on cleft risks, but all suffered from data and design limitations. The interventional studies for human recurrence have serious flaws, particularly in lacking a real control group generated by a randomization and in using combined interventions that do not allow for isolating the effects of folic acid
[120]. Control subjects in these studies were usually women who either refused or did not comply with the intervention
[116,117] or are otherwise poorly defined. This increases the chance of biases due to self or researcher selection of treatment, which confound the study results and introduces outcome differences that are not necessarily generated by the intervention. The different supplements and folic acid dose combinations make it hard to compare results and to attribute effects specifically. The sample sizes employed in these studies were also small and overall only borderline statistical significance was observed.

Observational case–control studies also have inherent problems, including non-random self or provider selection of supplement use. This is in part determined by perceived health risks that may also affect the risk for clefts. For example, women with unfavorable pregnancy histories, health problems or a family history of birth defects may use more folic acid but may also have a greater risk of poor pregnancy outcomes including CL/P. Further confounding results from the lack of data on health behaviors that may be correlated with both supplement use and oral cleft occurrence. Other limitations include potential bias in self-reported use of supplements and the lack of a well defined regimen for vitamin content, dose, and time of use. While helpful for exploratory research purposes, observational studies are not sufficient for answering the research hypothesis posed in this study.

Only a double-blinded, randomized experimental study, with sufficient sample sizes, can provide the opportunity to clearly address our hypothesis. The objective of this study is to assess the effect of folic acid supplementation of 4 mg/day taken at preconception and throughout the first three months of pregnancy on reducing the recurrence of CL/P compared to a 0.4 mg/day standard dose among women born with CL/P or mothers of children with CL/P using a double blinded randomized clinical trial design.

This study has the ability to identify, for the first time, the true preventive effects of folic acid on recurrence of oral clefts, using a dose that has proved effective in preventing recurrences of NTDs
[118]. The double blind randomized design will cleanly separate the effect of the intervention from those confounding effects that have plagued previous interventional and observational studies. This study provides the chance to evaluate a treatment that if successful, will determine the standard of care for high risk women in the United States and abroad.

## Methods/design

### Study design

#### Objectives

The overall goal of this randomized, double-blinded study is to reduce the recurrence of non-syndromic cleft lip with or without cleft palate (NSCL/P) in a high-risk group of women supplemented with folic acid from preconception and continuing throughout the first three months of pregnancy.

#### Design

Subjects will be randomly assigned to 4 mg or 0.4 mg pills of folic acid (identical in appearance). A single pill of 4 mg or 0.4 mg of folic acid will be taken daily until pregnancy is documented. Once pregnancy is documented, the trial drug will be continued until 3 months after the last menstrual period. At this point, the trial drug will be discontinued and women will take routine prenatal vitamins until delivery following routine obstetric care. At the end of the study, recurrence will be assessed and compared between groups. The total sample recurrence rate as well as recurrence rates that are specific to the 0.4 mg and 4 mg folic acid groups will also be compared to the recurrence rates of oral clefts in a historical control group.

#### Primary hypothesis/primary outcome

The primary hypothesis is that folic acid supplementation of 4 mg/day at preconception and during the first three months of pregnancy will decrease the recurrence of NSCL/P in a high risk (history of NSCL/P in mother or child) group of women when compared to women taking 0.4 mg per day of folic acid. The primary outcome measure will be the difference in NSCL/P recurrence rates between the two groups and the associated confidence interval. The study is powered to detect a 50% reduction at a 0.8 power.

#### Secondary hypotheses

The following secondary hypotheses will be evaluated:

An increase in serum and/or red cell folate levels in all women following daily supplementation with folic acid.

When compared to the 0.4 mg supplemented groups, the 4 mg per day group will have the following:

‐Greater increases in serum and/or red cell folate.

‐Decreases in the recurrence of NSCL/P in each of the following subgroups:

•Women with NSCL/P themselves

•Women with one or more children with NSCL/P

‐A decrease in the severity of NSCL/P in offspring of trial mothers.

‐No increase in twinning rates.

No increase in miscarriage rates.

No increase in rates of preeclampsia.

‐No increase in rates of other birth defects.

‐No decrease in birth weight

‐No decrease in gestational age

A decrease in recurrence of NSCL/P in the group of study subjects compared to an historical control group obtained from the populations served by the craniofacial clinics participating in the study.

A greater decrease in the recurrence of NSCL/P in the group of study subjects receiving 4 mg of folic acid when compared to the historical control group relative to that of the group receiving 0.4 mg when compared to the same control group.

Under separate funding we will examine the role of genes involved in folate metabolism on folate, B12 and homocysteine levels, as well as potential interaction between these genes and the supplementation dose. This project will also establish a resource to examine the long-term outcomes of infants exposed to high dose folic acid in utero.

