### Statistical analysis

#### Analysis plan

An intention to treat analysis will be first applied to test the primary and secondary outcomes of the study, where each randomized subject that contributes an informative observation to these outcomes (e.g. a birth) will be included in the analysis, regardless of compliance with study pills or follow-up schedules. Accordingly, randomized subjects will not be purposefully excluded from the study except if they become permanently sterilized or in the unexpected cases where they may no longer take folic acid due to a significant health problem (e.g. allergy to folic acid). The first analysis for the primary hypothesis will exclude subsequent births for subjects who continue to participate in the study after giving birth in the study as these multiple observations will be correlated yet these will be included in secondary analyses that account for multiple observation correlation as further described below.

Due to the randomized design of the study and the large sample sizes, the two treatment groups are expected to be equivalent for factors that may affect recurrence of CL/P and the other secondary outcomes. Therefore, the effects of the treatment dose on study outcomes will first be analyzed using simple bivariate tests such as Fisher’s exact test for rate differences (e.g. CL/P recurrence) and means test for continuous outcomes (e.g. folate levels). The primary estimated effect of the 4 mg folic acid dose compared to 0.4 mg on CL/P recurrence will reflect an average estimate across the two risk groups of women with CL/P and mothers of children with CL/P, but we will also evaluate potential interaction between the dose effect and risk group (such as by using a chi-square test for a common odds ratio across the two groups) and test for the effect of the intervention separately in the two risk groups (though at reduced power).

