This study may also allow evaluating secondary outcomes. The effect of the intervention on severity of clefting will be assessed. We will also stratify our analysis to examine differences in outcomes in the women born with CL/P independently from women who have a child with CL/P. The data from previous studies suggest a similar affect of folic acid supplementation in mothers with CL/P when compared to mothers who had a child with CL/P but as described below we will examine the groups together and separately.

Table
9 lists a few plausible effects and changes between the 4 and 0.4 mg groups and the total number of births needed to observe those effects with 80% power (type I error of 5%). Each of these (and others) will be studied as secondary outcomes. The DSMB will also monitor these outcomes to determine if significant untoward side effects are occurring (increases in miscarriage rates for example) but this is done independently of the research staff. All power simulations are based on a two-sided test except for the severity measure which is based on a one-sided test given that severity is expected to decrease with the higher dose.

**Table 9 T9:** Power to evaluate secondary outcomes

**Secondary outcome**	**Total births**
Birthweight (difference of 100 gm)*	928
Birthweight (difference of 200 gm)*	234
Gestational age (difference of 2 days*	2484
Gestational age (difference of 4 days*	622
Pre-eclampsia-Change by 40% from 10% baseline rate	1540
Pre-eclampsia-Change by 50% from 10% baseline rate	948
Severity (50% change from cleft lip with palate to cleft lip only in affected cases with 25% overall cleft prevention)	680
Miscarriage (30% change from 15% baseline rate)	1629
Miscarriage (50% change from 15% baseline rate)	562
* Assumes SD of 543 grams (birthweight) and 17.8 days (gestational age) as estimated in our studies in these populations.	

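### Six secondary hypotheses claim absence of harm from 4 mg, but the tests named for them look for a difference and no margin is set, so a non-significant result could not support those claims

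*Protocol article*

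**What the plan says.** Under Secondary hypotheses, the protocol article compares 4 mg with 0.4 mg and states six expectations of no harm. Four concern rates: "No increase in twinning rates", "No increase in miscarriage rates", "No increase in rates of preeclampsia" and "No increase in rates of other birth defects". Two concern continuous outcomes: birth weight should not fall, and "No decrease in gestational age".

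The Analysis plan section says the primary and secondary outcomes will first be analysed with "simple bivariate tests such as Fisher’s exact test for rate differences (e.g. CL/P recurrence) and means test for continuous outcomes". Weighted analyses and adjusted regressions follow as secondary analyses. None of these is given a margin.

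The Power analysis section sizes several of these outcomes in Table 9 as changes or differences to be detected with 80% power at a 5% type I error: "All power simulations are based on a two-sided test except for the severity measure". Twinning and other birth defects have no row in Table 9. A confidence interval is named only for the primary outcome (Primary hypothesis/primary outcome).

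**The concern.** A hypothesis of no increase is a claim that any harm is smaller than some tolerable amount. Fisher's exact test and a means test both take equality as the null. Rejecting that null shows a difference. Failing to reject it leaves both no effect and a real harm open. The named tests therefore cannot confirm the stated hypotheses at any sample size, and the rarer the event, the more easily a non-significant result arises.

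The stakes are stated in the article itself. Objectives and significance of proposed study says a successful result would determine the standard of care for high-risk women, and Related risks names miscarriage and twinning as suggested but unconfirmed risks of folic acid. A statement of no increase resting on a non-significant test would feed into that decision without support.

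**Working it through.** **Inputs from the article.** 1,582 births split equally, so 791 per arm (Power analysis). Pre-eclampsia baseline 10%, miscarriage baseline 15%, SD 543 g for birth weight and 17.8 days for gestational age (Table 9). Two-sided 5% test.

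**Reproducing Table 9.** For means, total n = 4 × [(1.96 + 0.8416) × SD / d]².
- 2 days: 4 × [2.8016 × 17.8 / 2]² ≈ 2,487. The row "Gestational age (difference of 2 days" gives 2,484.
- 4 days: about 622 (stated 622).
- 100 g: about 926 (stated 928).

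The 40% pre-eclampsia row (1,540) reproduces as 1,542 with a two-sided, continuity-corrected formula for 10% versus 6%, which is a decrease. For 10% versus 14%, the direction the hypothesis concerns, the same formula gives 2,170. The article's own sizing is thus about detecting a difference.

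**Chance of a non-significant result when harm is real, continuous outcomes.** SE = SD × √(2/791); miss probability ≈ Φ(1.96 − d/SE).
- 2 days: SE = 0.895, d/SE = 2.235, Φ(−0.275) = 39%.
- 4 days: d/SE = 4.469, miss 0.6%.
- 100 g: SE = 27.30, d/SE = 3.662, miss 4.4%.

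**Rates.** The probability of every pair of event counts with Fisher p ≥ 0.05 was summed exactly, with binomial counts at 791 per arm.

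| Outcome | True change | Missed | Baseline |
|---|---|---|---|
| Pre-eclampsia | 10% to 14% | 34% | Table 9 |
| Pre-eclampsia | 10% to 15% | 16% | Table 9 |
| Miscarriage | 15% to 19.5% | 36% | Table 9 |
| Miscarriage | 15% to 22.5% | 3.5% | Table 9 |
| Twinning, doubled | 1.5% to 3% | 54% | assumed |
| Twinning, doubled | 1% to 2% | 71% | assumed |
| Twinning, doubled | 0.8% to 1.6% | 77% | assumed |
| Other defects, 1.5-fold | 5% to 7.5% | 50% | assumed |
| Other defects, 1.5-fold | 3% to 4.5% | 70% | assumed |
| Other defects, 1.5-fold | 2% to 3% | 80% | assumed |

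**If the targeted subject-years are reached.** 18,897 × 0.0957 = 1,808 births, plus the 50 already observed = 1,858, or 929 per arm. The misses become 26% (pre-eclampsia 10% to 14%), 29% (miscarriage 15% to 19.5%) and 32% (2 days). Counting miscarriage per pregnancy at the minimum size gives nearly the same denominator: 1,582 / 0.85 = 1,861 pregnancies, 930 per arm, miss 29%.

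**What an interval could show.** With equal true rates, the 95% half-width is 1.96 × √(2p(1−p)/791): 0.98 points at 1%, 1.68 at 3%, 2.96 at 10% and 3.52 at 15%. At an assumed 1% twinning rate, even a near-doubling could not be excluded when the observed rates are equal.

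**The case against.** A reader might infer that the plan will treat p > 0.05 as proof of safety. The article does not say so. The bivariate tests are introduced as examples, the examples given are cleft recurrence and folate, and the adjusted regressions would yield effect estimates. Power analysis also has the data and safety monitoring board look for untoward effects, which is a detection aim that a two-sided test fits. That reading is therefore not claimed here. What stands is that the stated hypotheses are of no harm and the named tests cannot support them.

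A reader might also infer that real harms would usually be missed. On the effect sizes in Table 9 they would not: every such harm computed above is detected more often than missed. Misses above 50% depend on assumed baselines for twinning and other defects, and 1,582 births is the minimum rather than the target.

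Margins and reporting rules can properly be left to an analysis plan or full protocol, neither of which is shown, so their absence alone is no finding. But the form of the hypotheses and the type of test are fixed here, and they do not match.

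The board does monitor miscarriage, twinning and pre-eclampsia, with an unquantified threshold mentioned for the first two (Related risks; Interim analysis and study monitoring). That protects participants during the trial. It is not a final test of no increase.

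**Conclusion.** The concern holds as a mismatch between six absence-of-harm hypotheses and tests of difference. On the article's own figures, moderate harms would go undetected in 34% to 39% of trials at 1,582 births, and in 26% to 32% at about 1,858. For twinning and other birth defects the range is 50% to 80% at 1,582 births, resting on baselines of 0.8% to 1.5% and 2% to 5% that are assumptions, because the article gives none. Losses of 100 g and 4 days are well covered. The calculations assume equal arms, independent births and the Table 9 SDs. The point concerns secondary outcomes and leaves the primary comparison untouched, but it should be corrected because the safety conclusion bears on whether the high dose is recommended.

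**What to change.** In Secondary hypotheses and Analysis plan, restate the six items as safety outcomes. Report each as the 4 mg minus 0.4 mg difference with a two-sided 95% confidence interval, and state that a non-significant result is not evidence of no harm. Conclude no increase or no decrease only where the confidence limit on the harm side excludes a margin that the investigators have justified and fixed before unblinding. Otherwise report the outcome as inconclusive.

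The Table 9 effects should not become margins by default. They are differences the trial hoped to detect, and nothing in the article calls a 4-point rise in pre-eclampsia or a 4.5-point rise in miscarriage tolerable.

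The change is to wording and reporting; it needs no extra participants or data. The cost is that several outcomes will probably be inconclusive, above all twinning and other birth defects. As an illustration only, with no true difference and an assumed 1% twinning rate, a 1-point margin would be excluded only about 52% of the time at 791 per arm. Where no margin can be justified, give the estimate and interval and drop the claim.

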#### Historical control group

The recurrence rates in this study will be compared to that of an historical control group. The rationale for using this group relates to the inability to use a placebo control in this study due to ethical considerations. A comparison with an historical control group will allow the assessment of the combined effect of a minimum dose of folic acid of 0.4 mg and a maximum dose of 4 mg by comparing the NSCL/P recurrence rate in the total study group to that of a group of women who did not receive the folic acid dose of 0.4 mg per day. The effect of each of the two folic acid doses on the recurrence risk of NSCL/P could also be evaluated by comparing the NSCL/P rate in each of the two study groups (0.4 mg and 4 mg folic acid) to that of the historical control group.

The historical control will include women with NSCL/P or mothers of children with NSCL/P who are registered at the craniofacial clinics enrolled in the study. Those clinics have been involved in the provision of services to subjects with clefts for an extensive period, thus rates of cleft recurrence can be calculated over an extended time course providing not only cross-sectional data but also trends data adding to the validity of the historical control approach. Such data will reveal any changes in recurrence rates that might have occurred over time.

Taking into consideration the traditional internal validity challenges associated with using historical controls, no major historical events that could affect recurrence rates of NSCL/P in this population are expected to have occurred during the years immediately preceding this study.

Since the two randomized study groups (0.4 mg and 4 mg folic acid) will be compared to the same group of historical controls, any differences in the relative decreases of NSCL/P recurrence rates that may be observed between each of the study groups and the historical control group can be safely attributed to the effect of administered folic acid.

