#### Control group

The control group in this study will be the 0.4-mg folic acid group. A placebo control group is not used, as a low dose of folic acid is already recommended as a standard vitamin therapy for women during preconception and pregnancy period.

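### The historical controls are labelled as not having received 0.4 mg folic acid, but nothing in their selection secures this, so the comparison cannot give either dose's effect against no supplement

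*Protocol article*

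**What the plan says.** The section on the historical control group explains that a placebo was ruled out on ethical grounds and that a historical comparison will be used. It describes the comparator as "a group of women who did not receive the folic acid dose of 0.4 mg per day". It says the comparison with the total study group will show the combined effect of doses from 0.4 to 4 mg, and adds: "The effect of each of the two folic acid doses on the recurrence risk of NSCL/P could also be evaluated".

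The same section says who the controls are: "women with NSCL/P or mothers of children with NSCL/P who are registered at the craniofacial clinics enrolled in the study". On the period it says only that "rates of cleft recurrence can be calculated over an extended time course". It gives no criterion on folic acid use and no dates.

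The Control group section, under Study interventions, gives the reason for having no placebo arm: "a low dose of folic acid is already recommended as a standard vitamin therapy for women during preconception and pregnancy period". The objectives describe the randomised comparison as 4 mg "compared to a 0.4 mg/day standard dose among women born with CL/P".

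Two of the secondary hypotheses use the historical group. The first expects lower recurrence in all study subjects than in the controls. The second expects a larger decrease against the controls for 4 mg than for 0.4 mg.

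**The concern.** The label and the selection rule describe different groups. The label says the women did not receive 0.4 mg per day. The rule admits any registered woman with the right cleft history, whatever she took. The Sampling section names diagnosis, age and residence as the information searched for in clinic records and does not mention supplement use. The reason given for omitting a placebo, that low-dose supplementation is already recommended, is also a reason to expect that some controls took it.

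The protocol treats personal vitamin use as relevant: the Analysis plan lists other vitamin use among the factors that may affect recurrence and will be adjusted for.

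At stake is what the trial may report. Followed as written, it could publish an effect of 0.4 mg, or of each dose, against no supplement, from a comparator whose exposure is unknown. A real effect of the standard dose could be understated.

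**Working it through.** **The plan's own figures.** The article gives no size, rate or power for the historical comparison, so there is nothing to reproduce there. The 1,582 births in the Power analysis belong to the randomised comparison (5% against 2.5%, one-sided 5%, 80% power). A continuity-corrected calculation returns 1,584, close enough to confirm the figure. This point does not touch it.

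**Inputs.**
- p0: recurrence with no supplement. It cancels below.
- r: risk ratio of 0.4 mg against no supplement. Not in the documents; assumed 0.7 (a true 30% reduction), with 1.0 as the no-effect case.
- Risk ratio of 4 mg against 0.4 mg: 0.5, the reduction the study is powered for.
- u: share of historical controls who took 0.4 mg. Not in the documents; assumed 10% to 50%.
- Historical users are assumed to have the same benefit as the 0.4 mg arm.

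**Formulas.**
- Historical rate: h = p0 × [1 − u(1 − r)]
- Apparent reduction, 0.4 mg: 1 − r / [1 − u(1 − r)]
- Apparent reduction, 4 mg: 1 − 0.5r / [1 − u(1 − r)]
- Apparent reduction, both arms pooled equally: 1 − 0.75r / [1 − u(1 − r)]

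**Results for r = 0.7.**

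| u | 1 − u(1 − r) | 0.4 mg | 4 mg | Pooled |
|---|---|---|---|---|
| 0 (true) | 1.00 | 30.0% | 65.0% | 47.5% |
| 0.1 | 0.97 | 27.8% | 63.9% | 45.9% |
| 0.2 | 0.94 | 25.5% | 62.8% | 44.1% |
| 0.3 | 0.91 | 23.1% | 61.5% | 42.3% |
| 0.5 | 0.85 | 17.6% | 58.8% | 38.2% |

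Example: at u = 0.5, 0.7 / 0.85 = 0.824, an apparent reduction of 17.6%.

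**No-effect case.** With r = 1, h = p0 at every u. The apparent reductions are 0% for 0.4 mg and 50% for 4 mg, both correct. Mixed use dilutes only if 0.4 mg itself lowers recurrence.

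**Second historical hypothesis.** Both arms are set against the same h. The ratio of the two risk ratios is (p4/h) / (p0.4/h) = p4/p0.4, and the difference of the absolute decreases is (h − p4) − (h − p0.4) = p0.4 − p4. The control rate cancels in both. The difference of the relative decreases is (p0.4 − p4)/h, where h rescales the size but cannot change the sign or create an effect. This hypothesis reduces to the randomised contrast.

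**The case against.** The best defence has four parts.

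1. A recommendation is not uptake. The statement is in the present tense and gives no start date and no share of users. This stands: the size of any dilution is unknown, and the range above is assumed.

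2. The controls cover an undated extended period and may include births before the recommendation, or women with little access to supplements. This also stands. A reader might infer that the controls must be either a mixture of users or self-selected non-users; the documents do not support that split. But unexposed women from an earlier era differ from trial women by period, so the each-dose reading would still not be secured.

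3. A low dose may do nothing for clefts. The article's review of earlier trials and of fortification leans that way for occurrence, and mixed use would then cause no dilution. That is right as arithmetic. However, the effect of 0.4 mg is one of the things this comparison is meant to show, so it cannot be assumed in advance.

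4. The claim is secondary and partly hedged: each dose's effect is said only to be something that could be evaluated, and the section acknowledges the usual validity problems of historical controls. This limits the weight of the point. It does not reconcile the label with the selection rule.

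A reader might also infer that the trial repeats a flaw the article criticises in earlier studies: "Control subjects in these studies were usually women who either refused or did not comply with the intervention". The documents do not support this. The rule here is a clinic registry with no criterion of non-use, and nothing says controls will be chosen because they declined a supplement. Any estimate of false claims from such selection would need a design and inputs that the protocol does not state.

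**Conclusion.** The point holds in a limited form. The article calls the historical controls unexposed to 0.4 mg per day, its selection rule does not secure that, and the same article calls that dose the recommended standard. The arm-versus-historical contrasts cannot be read as the effect of each dose, or of at least 0.4 mg, against no supplement.

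The size depends on two quantities the documents do not give. With assumed uptake of 10% to 50% and a true 30% reduction for 0.4 mg, the apparent reduction is about 28% down to 18%; if 0.4 mg has no effect, the dilution is nil. In this mixture model the bias is towards no difference.

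The first historical-control hypothesis and the each-dose statement are affected. The comparison of the two decreases is not, because it shares one control rate, and the randomised primary analysis, its sample size and its error rate are untouched. The wording should be corrected before the historical comparison is reported.

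**What to change.** In the Historical control group section:

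- Describe the controls as women under past usual practice at the same clinics, whatever their supplement use.
- State that the contrast estimates trial supplementation against past usual practice.
- Delete the statements that it gives the effect of a minimum dose of 0.4 mg, or of each dose against no supplement.
- Add a small sensitivity table over assumed uptake, in the form shown in the working, including the case where 0.4 mg has no effect.
- Say that conclusions about dose rest on the randomised comparison.

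This needs a few sentences and one table. No new data, sample size or primary analysis is involved. The downside is a narrower secondary claim.
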